**Fig. 3 fig3:**
[figure not shown]
Required sample size expecting small-to-medium effect of the intervention.

We decided to aim for a total sample of 100 participants, which will allow us to detect effects as small as f2 = 0.075 with power of 0.8. Importantly, this sample size also allows us to have reasonable confidence in detecting small-to-medium effects (e.g., f2 = 0.1) assuming a drop out rate as large as 30 % (i.e., final n = 70), which is important for per-protocol analyses.

Secondary analyses will explore nutrition's impact on health and wellbeing in children with CP, focusing on four key areas:1.Anthropometric Measures: Beyond the primary measure of Weight for Age Z-score (WAZ), we will use BMI, skin fold thickness, and mid-upper arm circumference, using age-standardized z scores, to assess the robustness of our conclusions about the effectiveness of the intervention across anthropometric indicators of nutritional status.2.Biochemical Indicators: Analyzing Vitamin D and iron levels to identify changes in nutritional deficiencies between intervention and control groups.3.Healthcare Utilization: We'll assess health indexes such as bedridden days, emergency visits, infections, hospitalizations, and impact on regular activities and family life, comparing improvements between the intervention and control groups.4.Behavior and Quality of Life: Investigating changes in child behavioral functioning and family quality of life to determine if the intervention group shows greater improvements compared to the control group.

These analyses will deepen our understanding of the nutritional intervention's broader impacts on children with CP and their families.

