## Planned analyses

4

The outcomes of the intervention will be assessed using both Intention-to-Treat (ITT) and Per-Protocol (PP) approaches. In the ITT approach, analyses include all study participants who were randomized to either of the study arms. In the PP approach, the analyses are restricted to participants who adhere to the protocol. We will not perform any imputation for missing data. Typically, the ITT method is favored for trials aiming to demonstrate superiority or non-equivalence (such as our study), PP approach is more suitable for trials assessing equivalence or non-inferiority Ahn et al., [15]. Nonetheless, it is advisable to execute both methods of analysis and compare their outcomes to identify any notable discrepancies. Employing both the ITT and PP strategies offers a fuller understanding of the effects of the treatment and enhances the credibility of the trial findings. In the case of the ITT analysis, we will focus on Weight for age Z-score (WAZ) (based on WHO standards 2006–2007) [16]. As WAZ is a standardized score for an individual given population norms, we anticipate the intervention to produce change at the tails of the distribution (for children outside the normal range) rather than the center (children in the normal range). This suggests that, in the intervention group, the baseline WAZpre variable may have a cubic relationship with the outcome WAZpost variable (Fig. 2).

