### Sample size calculation

4.1

Sample size calculations are based on assuming that 1) is the best fitting model. While it is desirable to base sample size on the most complex model used in the analyses, given that 1) it is unclear which model will show best fit to the data, and 2) estimates of sample size for regression models including interactions require understanding of the correlations between the variables, an understanding that we currently do not have, this approach was deemed warranted.

Sample size calculations were conducted in G*Power 3.1 1 Fig. 3 shows the sample size calculations assuming that 1) the effect of the intervention will be small to medium, and 2) a two-sided significance test.

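### Section 4.1 states 80% power for f2 = 0.075 with 100 children; at two-sided 5% the figure is 77%, and the drop-out allowance is tied to per-protocol analyses although it also affects the ITT regression

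*Protocol article*

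**What the plan says.** Section 4.1 of the protocol article gives the basis of the calculation: "Sample size calculations were conducted in G*Power 3.1", and "Sample size calculations are based on assuming that 1) is the best fitting model". Model (1) regresses the 6-month WAZ on Treatment and baseline WAZ. The test is described as "a two-sided significance test". The calculation itself is left to Fig. 3, which is not reproduced in the text available, and no alpha appears in the readable text.

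The conclusion follows under Fig. 3. The target is 100 children in all, and the text says of this number: "which will allow us to detect effects as small as f2 = 0.075 with power of 0.8". The next sentence considers drop-out of up to 30%, leaving 70 children. It moves to a larger effect, f2 = 0.1, and expresses reasonable confidence in detecting it without giving a power. It then adds "which is important for per-protocol analyses".

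Section 4 (Planned analyses) says that ITT is the favoured approach for a superiority trial such as this one, that it includes everyone randomized, and that its focus is WAZ. It also says "We will not perform any imputation for missing data". Table 1 (section 3.4) schedules anthropometry at baseline and at the 6-month visit only.

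**The concern.** This is the only power statement for the primary outcome, and two things about it look wrong.

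- The stated 0.8 can be checked, because N, f2, the model and the sidedness are all on the page. With the usual alpha it comes out lower.
- Drop-out is brought in as a per-protocol consideration. A regression on the 6-month WAZ without imputation can use only children who have a 6-month WAZ, so the ITT analysis loses the same children.

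At stake is what the trial says it can detect. A reader would take f2 = 0.075 as the 80%-power effect of the primary analysis, when the analysed sample may support only a clearly larger one.

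**Working it through.** **Inputs**

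- N = 100, f2 = 0.075, stated power 0.8: section 4.1.
- Two-sided test, G*Power 3.1, model (1) with two predictors and one tested coefficient (Treatment): section 4.1 and model (1) in section 4.
- 1:1 allocation: section 3.5.
- 30% drop-out, 70 remaining, f2 = 0.1: section 4.1.
- Alpha: not in the readable text; two-sided 0.05 assumed.

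**Formula**

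Power = P(F′ > F_crit), where F′ is noncentral F with 1 and N − 3 degrees of freedom and noncentrality λ = f2 × N, and F_crit is the 95th centile of the central F with the same degrees of freedom. This is the fixed-model test of one regression coefficient and is taken to be the plan's method.

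**Step 1: the plan's own figure**

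λ = 0.075 × 100 = 7.5; df = 1 and 97; F_crit = 3.94. Power = 0.774, which is 2.6 points below the stated 0.80.

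**Step 2: what gives 80%**

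- At f2 = 0.075: N = 106 gives 0.798 and N = 107 gives 0.801, so 107 analysed children are needed.
- At N = 100: solving for f2 gives 0.080.
- With equal arms f2 = d²/4, so d = 2√f2 in residual SDs between arms: 2√0.075 = 0.55 against 2√0.080 = 0.57.

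**Step 3: other readings of the stated 0.8 (N = 100)**

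| Reading | Power |
|---|---|
| Model (1), two-sided 0.05 | 0.774 |
| One predictor / five predictors | 0.774 / 0.7735 |
| Normal approximation | 0.782 |
| Joint test of both coefficients | 0.673 |
| One-sided 0.05 (same as two-sided 0.10) | 0.859 |
| Two-sided alpha 0.06 | 0.798 |
| 0.075 read as partial R² (f2 = 0.075/0.925 = 0.081) | 0.805 |

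Two readings come close to 0.80. One is an alpha of 0.06, to which nothing in the text points. The other takes 0.075 as a partial R², whereas the text says f2.

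**Step 4: drop-out**

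| Analysed N | λ at f2 = 0.075 | Power at f2 = 0.075 |
|---|---|---|
| 100 | 7.50 | 0.774 |
| 90 | 6.75 | 0.729 |
| 80 | 6.00 | 0.677 |
| 70 | 5.25 | 0.617 |

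At the plan's own pairing, f2 = 0.1 with 70 children, λ = 0.1 × 70 = 7.0 and power is 0.741. The effect detectable with 80% power at 70 is f2 = 0.115, or 2√0.115 = 0.68 residual SD.

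**Step 5: which analysis loses the children**

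The outcome in models (1) and (2) is the 6-month WAZ. Table 1 has no anthropometry between baseline and 6 months, and section 4 rules out imputation. A child without a 6-month weight contributes no outcome to either regression. Of the children randomized, the ITT regression therefore keeps only those with a 6-month weight, and the 70-child scenario can apply to it as well.

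**The case against.** **The inputs are partly out of sight.** Fig. 3 is not shown and may state alpha. This stands as a condition on every figure here, although two-sided 0.05 is the natural default.

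**The slip may be in the label.** If 0.075 was entered as a partial R², power is 80.5% and the power itself is not overstated. This also stands as a possibility. It does not rescue the sentence, which would then give the wrong effect measure.

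**The gap without drop-out is minor.** It is 2.6 power points, seven children, or 0.57 against 0.55 residual SD. The normal approximation gives 78.2%, and a value read off a plotted curve could differ by this much. A null result would in any case be read from its confidence interval. All of this is fair, and it limits the weight of the point.

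**The plan did consider attrition.** A reader might infer that the plan claims 80% power for f2 = 0.075 with 70 children and that 62% refutes it. The text makes no such claim: at 70 it turns to f2 = 0.1 and gives no number. About 74% does not contradict an expression of reasonable confidence. The 62% is a sensitivity figure at the plan's largest drop-out, for an effect size the plan did not pair with it.

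A reader might also infer that the plan says drop-out affects per-protocol analyses alone. It does not say so. It mentions drop-out in that connection and is silent on ITT. What survives is that this silence leaves the power of the favoured analysis described only for complete follow-up.

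**Conclusion.** The point holds as a moderate correction.

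From the stated f2, model (1) and a two-sided test at an assumed 5%, 100 analysed children give 77% power rather than 80%. The detectable effect at 80% is f2 = 0.080. The sentence needs correcting whether the power or the effect-size label is at fault.

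The drop-out part carries more weight. With no imputation and weight taken only at 0 and 6 months, losses reduce the ITT regression as well. At the plan's upper figure of 30%, the effect detectable with 80% power rises to f2 = 0.115, about one and a half times the stated 0.075 (0.115/0.075 = 1.5).

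These figures rest on alpha 0.05, on model (1) being the model reported, and on drop-out meaning no 6-month weight. None of this shows that the enrolment target must change.

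**What to change.** Check the G*Power output behind Fig. 3 for the alpha and the effect measure that were entered. If they are two-sided 0.05 and f2, replace the power sentences in section 4.1 with:

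> With 100 analysed children and two-sided alpha 0.05, model (1) has 80% power for f2 = 0.080 (77% for f2 = 0.075). With 30% drop-out (70 analysed) it has 80% power for f2 = 0.115, 74% for f2 = 0.10 and 62% for f2 = 0.075. Because missing outcomes are not imputed, the drop-out figures apply to the primary ITT analysis as well as to the per-protocol analysis.

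If a different alpha or a partial R² was used, state that and recompute the figures on the same basis.

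The cost is one paragraph of wording and a slightly less favourable figure. Enrolment, design and analysis stay as they are.

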## Data management

5

We will implement a strict data management strategy to ensure data integrity, confidentiality, and reliability. Data will be securely collected electronically, with entry by trained personnel. Our protocol adheres to Ref. [19] guidelines and the Declaration of Helsinki, and it has received ethical approval by the Medical Ethics Committee at the Medical University of Varna (Protocol No. 134 dated 20.07.2023). Informed consent will be obtained from parents or guardians after providing them with thorough information about the study. Data privacy is a priority and access will be restricted to authorized personnel. To mitigate bias, the statistical analysis will be blinded. Group identifiers will be replaced with neutral codes by an independent data manager before data analysis. The analyst will conduct the analysis without knowledge of group identities, which will only be revealed after the primary analysis is complete. This blinding process will be thoroughly documented, and an independent statistician will verify the analysis to ensure its integrity. The study is registered on clinicaltrials.gov (NCT06065904).

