### Intervention

3.6

*Nutritional Intervention Arm* The baseline comprehensive nutritional assessment will lay the groundwork for a tailored nutrition plan informed by the assessment outcomes and guided by the national nutrition recommendations for children in Bulgaria [11], registered dietitians will develop personalized dietary recommendations for each child. These recommendations will be designed to address the unique dietary needs and challenges of each participant, taking into careful consideration their individual food preferences, sensitivities, and essential nutritional requirements. Adjustments in diet may include modifications to the texture, taste, and presentation of food, aiming to enhance food acceptance and meet nutritional goals. In certain cases, the introduction of dietary supplements, ranging from enteral formulas to fortified foods or more comprehensive measures like enteral nutrition, is recommended in accordance with ESPGHAN guidelines [12].

The support and monitoring of this intervention are carried out by qualified nutritionists or dieticians. This involves a structured follow-up mechanism that includes monthly phone check-ins and a comprehensive email consultation at the end of the third month. These interactions aim to address any nutrition-related concerns, assess adherence to the dietary recommendations, and make necessary adjustments. The adherence to the nutritional plan is further evaluated during a 6-month visit, primarily through the improvement in dietary intake as documented in a three-day food diary.

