### Standard care comparison

3.7

Participants assigned to the *Standard Care Arm* receive the conventional care typically provided to children with neurological impairments in their respective daycare or residential centers. This standard care encompasses a range of services, including regular health check-ups, therapeutic services, and educational support, aimed at addressing the general needs of children with CP.

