**Fig. 2 fig2:**
[figure not shown]
Hypothetical form of the results for control group (green) and intervention group (blue). The figure captures the intended change for underweight and overweight children and the intended no change for children with weight in the normal range. (For interpretation of the references to colour in this figure legend, the reader is referred to the Web version of this article.)

As Fig. 2 suggests, the expected findings depend on the initial distribution of WAZ. An effect of the intervention may show as a main effect if the participants fall mainly at one end of the WAZ distribution, an interaction between Treatment and Baseline if baseline WAZ extends from one end of the WAZ distribution to 0, or an interaction between the cubed Baseline term and Treatment if baseline WAZ spans the entire WAZ distribution.

Thus, to analyze the change in WAZ, we will first identify the best fitting regression model, starting with [17]. The independent variable Treatment will be coded 0 (control - standard care arm) and 1 (intervention arm). Interaction and cubic terms will be then added, at each step assessing if a more complex model is warranted by the data, based on adjusted R-squared [18] shows the most complex model we expect to assess. We will report the results from the best fitting model.(1)$${WAZpost\;∼\;b}_{0+b1*Treatment+b2*WAZpre}$$(2)$$WAZpost\;∼\;b0+b1*Treatment+b2*WAZpre+b3*Treatment*WAZpre+b4*WAZpre^{3}+b5*Treatment*WAZpre^{3}$$

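### The article promises a blinded statistical analysis but guarantees it only until the primary analysis is complete, leaving the per-protocol and secondary analyses uncovered

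*Protocol article*

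**What the plan says.** Section 5 (Data management) gives blinding of the statistical analysis as the means of limiting bias. The device is stated: "Group identifiers will be replaced with neutral codes by an independent data manager before data analysis". The analyst works without knowing the groups, "which will only be revealed after the primary analysis is complete". An independent statistician then checks the analysis.

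Section 4 (Planned analyses) states: "The outcomes of the intervention will be assessed using both Intention-to-Treat (ITT) and Per-Protocol (PP) approaches". It ties the intention-to-treat (ITT) analysis to WAZ. For the per-protocol (PP) analysis it says: "In the PP approach, the analyses are restricted to participants who adhere to the protocol". The regression variable is defined as follows: "The independent variable Treatment will be coded 0 (control - standard care arm) and 1 (intervention arm". Terms are then added to the model, "at each step assessing if a more complex model is warranted by the data, based on adjusted R-squared".

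Section 4.1 calls WAZ the primary measure and lists four areas of secondary analysis: other anthropometry, biochemistry, healthcare utilization, and behavior with quality of life.

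Section 3.6 (Intervention) says of adherence: "The adherence to the nutritional plan is further evaluated during a 6-month visit", mainly from the three-day food diary. Section 3.7 says that controls "receive the conventional care typically provided to children with neurological impairments in their respective daycare or residential centers".

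**The concern.** The promise in section 5 covers the statistical analysis as a whole, while the rule that implements it protects only the primary analysis. Nothing in the article keeps the remaining analyses blind.

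Those analyses matter to the trial's conclusions. The secondary objectives in section 2.2 are bedridden days, development and quality of life, and the Discussion names fewer bedridden days and better quality of life as hypotheses. Development is scored from a caregiver interview (section 3.4), and quality of life from questionnaires, interviews and surveys (section 3.8.4). The article states no blinding of families or assessors, so blinding of the analyst is the only blinding it offers for these outcomes. It gives regression models for WAZ alone. On the text shown, choices of handling, transformation and subset are therefore more open for the secondary outcomes, and an analyst who knows the arms can be influenced by them.

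Two smaller points bear on whether the blind is secure. The published 0/1 coding names the arms, while section 5 promises neutral codes. And adherence is described only for the arm that has a nutrition plan, so adherence records could show who was in it.

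**Working it through.** The article gives no figure on this point to reproduce. The check sets the sections side by side and adds two calculations.

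**1. What the disclosure rule covers**

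| Analysis | Where planned | Blinding guaranteed by section 5? |
|---|---|---|
| ITT, WAZ | Section 4; WAZ is the primary measure in 4.1 | Yes |
| PP | Section 4 | Only if counted as part of the primary analysis; not stated |
| Four secondary areas | Section 4.1 | No |

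The rule fixes the earliest moment at which identities may be revealed. It does not place the PP or secondary analyses before or after that moment.

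**2. Can the models be fitted on neutral labels?**

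Replace T (Treatment) by T' = 1 − T in model (1):

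b0 + b1·T + b2·WAZpre = (b0 + b1) − b1·T' + b2·WAZpre.

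The fitted values are the same and only the sign of the treatment coefficient changes. The same holds up to model (2), as long as each interaction enters together with its own WAZpre term, as it does there.

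This was confirmed on one simulated data set (n = 100, 1:1; the parameters are illustrative and not taken from the article):

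| Model | Adjusted R², labels as given | Adjusted R², labels swapped |
|---|---|---|
| (1) | 0.8041 | 0.8041 |
| + Treatment×WAZpre | 0.8568 | 0.8568 |
| + WAZpre³ | 0.8881 | 0.8881 |
| (2) | 0.8948 | 0.8948 |

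In model (1), b1 was 0.508 and became −0.508, with |t| = 4.81 both ways. Model selection and two-sided tests therefore do not require knowing which arm is which.

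**3. Could PP exclusions expose the arm?**

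Suppose there are 50 children per arm (100 children at 1:1) and e of them are excluded for non-adherence. If every child were equally likely to be excluded, the chance that all e fall in one arm is

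P = 2·C(50, e) / C(100, e).

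| e | P |
|---|---|
| 3 | 0.242 |
| 5 | 0.056 |
| 8 | 0.006 |
| 10 | 0.001 |

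For e = 5: 2 × 2,118,760 / 75,287,520 = 0.056. If non-adherence could be recorded in the intervention arm only, about eight one-sided exclusions would be hard to put down to chance, and an analyst could infer the arm. Whether this arises depends on PP criteria that the article does not give.

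**The case against.** The strongest reply is that the primary analysis is properly protected, and that is what matters most. Section 5 provides neutral codes, an independent data manager and an independent statistician. It guarantees blinding through the primary analysis, and the secondary analyses are described as exploring wider effects. Limiting analyst blinding to the primary analysis is a defensible choice. This stands as far as the primary result goes. It does not remove the mismatch between an unrestricted promise and a restricted rule, and verification afterwards does not undo choices made with the arms known.

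A reader might go further and infer three things that the article does not support:

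- **The 0/1 coding defeats the neutral codes.** It does not. Section 4 defines the model, section 5 says what the analyst receives, and the label swap shows that the two can coexist.
- **PP membership reveals the arm.** This is an inference about criteria not shown, which an analysis plan may supply. Table 1 schedules the food diary at both visits without restricting it to one arm, and nothing says that the blinded analyst derives the PP set. A PP analysis run after the ITT analysis leaves the primary blind intact.
- **The codes are opened before every secondary analysis.** The text permits this but does not say it.

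**Conclusion.** The point holds as a limit on scope. Section 5 announces a blinded statistical analysis, but its rule secures blinding only through the primary analysis. The PP analysis and all four secondary areas, and with them every secondary objective in section 2.2, may be run unblinded.

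It would be wrong to conclude that the blinded analysis is unworkable; nothing in the article prevents a blinded primary analysis. Nor can the size of any bias be stated. Counting the secondary comparisons would not measure it, and the count would depend on how the listed items are split.

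The conclusion rests on two readings: that the primary analysis is ITT on WAZ, and that the article states no other blinding. If the PP analysis of WAZ is meant to belong to the primary analysis, it falls under the blind, but the handling of adherence records then matters more. This is an inexpensive improvement worth making. It does not threaten the primary result.

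**What to change.** Amend section 5 in three respects:

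1. **Timing.** Reveal group identities only after the ITT, PP and secondary analyses have been run and the independent statistician has verified them.
2. **PP set.** Have the independent data manager supply a yes/no PP flag, and keep adherence and follow-up call records out of the file the analyst receives.
3. **Labels.** State that the section 4 models are fitted on neutral labels, and that 0 = control and 1 = intervention is attached at unblinding.

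One limit remains. Section 4 expects a cubic pattern in the intervention arm, so an analyst may still guess the arm from the fitted curves, and neutral labels do not prevent that.

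The cost is a few sentences and a slightly later unblinding. The data manager and the statistician are already in the plan, and the label swap shows no loss in model selection or two-sided testing.
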